### Variables

The main outcome variables aligned with the study objectives include the length of stay in the emergency department (measured in minutes), the number and type of radiological tests requested, the performance of bedside ultrasound (POCUS), diagnostic concordance, and the patient’s satisfaction with the care received. Sociodemographic variables such as age, sex, and distance from home, as well as clinical and procedural variables, will also be collected.

A complete list of all study variables, including their measurement units or response categories, is provided in Table 2, grouped into thematic blocks: sociodemographic, clinical, diagnostic, and outcome variables.

**Table 2. T2:** Study protocol variables.

Block and variable		Unit or format	Notes or response options
Sociodemographic			
	Identification code	Alphanumeric	Unique ID per patient
	Gender	Categorical	Male or female or other
	Date of birth	Date (dd/mm/yyyy)	Age will be calculated
	Distance to home	Kilometers	Estimated by postal code
Clinical			
	Health problems	Free text or ICD-10^a^	Comorbidities
	Current medications	Free text	List of active treatments
	Vital signs	Numeric (per parameter)	BP^b^ (mm Hg), HR^c^ (bpm), EVA^d^, temperature (°C), SatO_2_ (%)
	Reason for consultation	Free text	Chief complaint
Care process			
	Attending doctor	Code or initials	Family physician ID
	Date or time of arrival	Time stamp	Format: dd/mm/yyyy hh:mm
	Date or time of discharge	Time stamp	Format: dd/mm/yyyy hh:mm
	Origin	Categorical	Self-referred or primary care or ambulance or other
	POCUS^e^ performed	Binary	Yes or no
	POCUS findings	Free text	Based on clinical protocol
	Other tests requested	Categorical or multiple	Blood tests or ECG^f^ or other
	Radiology test performed	Categorical	X-ray or formal ultrasound or CT^g^ or none
	Interconsultation	Binary	Yes or no; specialty if applicable
Outcome			
	Diagnosis	Free text or ICD-10	Final ED^h^ diagnosis
	Discharge referral	Categorical	Home or hospitalization or specialist or follow-up
	Length of stay	Minutes	Calculated from entry and discharge times
	Satisfaction questionnaire	Likert scale or categorical	1‐5 scale or qualitative responses
	Diagnostic concordance	Binary	Yes or no (based on follow-up or second opinion)

a
*ICD-10: International Classification of Disease, Tenth Revision.*

b BP: blood pressure.

c HR: heart rate.

d EVA: Escala Visual Analógica (VAS: visual analog scale).

e POCUS: point-of-care ultrasound.

f ECG: electrocardiogram.

g CT: computed tomography.

h ED: emergency department.

Table 3 shows the results of the satisfaction questionnaire based on the SERVPERF model.

**Table 3. T3:** Satisfaction questionnaire based on the SERVPERF model^a^.

Dimensions and questions		Score range (strongly disagree to strongly agree)
Tangible elements		
	The facilities are suitable for patient care	1-7
	Technological equipment is adequate	1-7
	The emergency department has sufficient capacity to attend to the population	1-7
Responsiveness dimension		
	If you have any questions, you will receive a response within a reasonable time	1-7
	The attention of the staff provides a fast and high-quality service	1-7
	You have been dealt with quickly and promptly	1-7
Reliability dimension		
	When staff commit to doing something within a certain time frame, it is fulfilled	1-7
	If you have a problem, the staff show an interest in solving it	1-7
	Staff perform the service well the first time	1-7
	Professionals are ready to help when they are needed	1-7
Security dimension		
	Staff behavior imparts confidence	1-7
	There is a capacity to resolve doubts accurately	1-7
	Staff are knowledgeable when responding to queries	1-7
Empathy dimension		
	Care is offered that responds to the needs of the users	1-7
	Staff care about your interests and needs	1-7
	The emergency service provides a solution to the health needs of users	1-7
Access dimension		
	The waiting time for service was adequate	1-7
	Waiting time for tests and results was adequate	1-7
	The overall waiting time was adequate	1-7

a Likert scale (1-7) from least to most satisfaction.

Table 4 shows the work schedule for the study protocol.

Potential harms will be defined as any adverse event or unintended consequence resulting from the use of bedside ultrasound by nonradiologist physicians. Harms will be assessed systematically, using a structured reporting form completed by the attending physician and monitored through follow-up at 1 month. Any serious adverse events will be documented and reviewed by the principal investigator and the ethics committee if needed.

**Table 4. T4:** Timeline of the study.

		Year 1												Year 2											
	Phase 0	1	2	3	4	5	6	7	8	9	10	11	12	1	2	3	4	5	6	7	8	9	10	11	12
Ultrasound training	✓																								
Literature review update		✓																							
Presentation of the research project in the emergency department			✓																						
Protocol development				✓	✓																				
Design of the data collection form					✓	✓																			
Training and consensus on key pathologies							✓	✓																	
Data collection									✓	✓	✓	✓	✓	✓											
Data cleaning, analysis, and results generation															✓	✓	✓	✓	✓						
Results dissemination and manuscript preparation																				✓	✓	✓	✓	✓	✓

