The sample will consist of patients over the age of 18 years presenting with abdominal pain in the emergency department, who will be assigned to the experimental group (POCUS is performed) or the control group (no clinical ultrasound is performed) consecutively. Patients readmitted for the same pathology will be ruled out. Patients will be invited by the investigators to participate freely, and the recruitment will end when the minimum sample size is reached in each cohort.

The inclusion and exclusion criteria are presented in Textbox 1.

Textbox 1.The inclusion and exclusion criteria.

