**Inclusion criteria**
Patients treated at the Emergency Department of Riotinto Hospital during the study and follow-up periodPatients presenting with acute de novo abdominal pain, defined as a clinical condition causing pain localized by the patient between the thorax and the pelvis. Additionally, patients must not have been admitted for the same condition in the previous 3 months.Age ≥18 yearsPatients with sufficient capacity to provide written informed consentExperimental group: Patients will be attended by physicians from the Emergency Department of Riotinto Hospital and by professionals with demonstrated training in clinical ultrasoundControl group: Patients will be attended by physicians from the Emergency Department of Riotinto Hospital and by professionals without demonstrated training in clinical ultrasound

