**Exclusion criteria**
Patients with readmission due to abdominal painPatients who leave the emergency department before completing carePatients followed in other regional health systems or private health carePregnant womenPatients with morbid obesityPatients with severe mental illnessPatients whose clinical severity prevents obtaining informed consentIntercurrent illness that makes participation impossible

The reasons for study discontinuation are as follows: (1) patient withdrawal, (2) withdrawal of informed consent, (3) death, (4) protocol violation, and (5) intercurrent illness preventing continued participation.

Informed consent will be obtained by the attending physician at the time of patient evaluation, prior to any study-related procedures.

For the sample size calculation, emergency department length of stay was used as the primary variable, as it is the only parameter that has been studied to date (19). A 25% reduction in the mean length of stay is expected in the intervention group compared with the control group. According to the multicenter trial [30], the mean length of stay for patients with nontraumatic abdominal pain in the emergency department was 5.2 (SD 3) hours. Assuming a 25% reduction (1.3 h) in the intervention group, with a 2-sided significance level of 0.05 and a power of 80%, and applying a Student *t*-test for independent samples, a minimum of 84 patients per group is required. Considering an anticipated 15% attrition rate, the total number of participants to be recruited will be 194 patients (97 per group).

There will be no randomization of the sample, as the 2 groups will receive the same care as normal for their pathology; however, in the experimental group, the intervention (clinical ultrasound) will also be carried out to test its effectiveness and assess whether it improves the quality of care. It is important to consider that clinical ultrasound is not a regulated ultrasound, but rather a response to a clinical question; therefore, it is not a complex intervention, and with the usual pressure of the service, it can be performed at any time of the year.

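### The plan does not say when a patient's group is fixed, so grouping by whether a scan was ever done can bias length of stay, and the listed variables could not reveal it

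*Protocol article*

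**What the plan says.** All references are to the protocol article.

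- **Group by procedure (Methods, Study Design and Setting).** Patients are "assigned to the experimental group (POCUS is performed) or the control group (no clinical ultrasound is performed) consecutively".
- **Group by professional (Textbox 1, inclusion criteria).** Experimental patients are seen by professionals with demonstrated ultrasound training; control patients are seen "by professionals without demonstrated training in clinical ultrasound". The plural leaves open whether the first, the last or any professional decides.
- **Allocation (text after Textbox 1).** "There will be no randomization of the sample, as the 2 groups will receive the same care as normal for their pathology".
- **Consent (same place).** "Informed consent will be obtained by the attending physician at the time of patient evaluation, prior to any study-related procedures". Group membership is not tied to this moment.
- **Variables (Table 2).** The introduction reads "A complete list of all study variables, including their measurement units or response categories, is provided in Table 2". The table has one attending-doctor entry ("Family physician ID") and one binary entry for "POCUS^e^ performed". Neither carries a time, and no operator is recorded for the scan. Only arrival and discharge are time-stamped.
- **Outcome (Table 2).** Length of stay is "Calculated from entry and discharge times", so all time before a scan counts.
- **Analysis (Statistical Analysis).** A t test and a multiple linear regression are planned for length of stay. No rule covers a change of doctor or a late scan.

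**The concern.** If the group is defined by an event that can happen at any point in the stay, and the groups are then compared on the length of that stay, a longer stay gives more opportunity for the event. This is the structure of immortal-time bias. Take a patient first seen by an untrained doctor who is still in the department when a trained doctor takes over and scans. Under the procedure definition this is a POCUS patient, and the whole stay counts in that group. A similar patient discharged before the takeover stays in control. Long stays leave control and enter POCUS, which can hide a real reduction.

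The same patient also meets both descriptions in Textbox 1, since professionals of both kinds attended.

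Adjustment for baseline covariates cannot repair a group formed after baseline. Without times, the analyst cannot count the affected patients or reclassify them. Length of stay is the variable that sized the study, and without randomization the group rule carries the whole comparison.

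**Working it through.** **1. The plan's own figure.** Inputs from the sample size paragraph: mean 5.2 h, SD 3 h, difference 1.3 h, two-sided 0.05, power 80%.

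n per group = 2 × (1.96 + 0.8416)² × 3² / 1.3² = 83.6, so 84. The stated 84 reproduces, and this point does not change it.

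**2. Assumptions, none of them in the documents.** Shifts of 8, 12 or 24 h; arrival uniform within a shift; half the doctors trained; every patient whose first doctor is trained is scanned; a trained doctor who takes over scans with probability q. Stays follow a gamma distribution with the plan's mean and SD. There is no true effect.

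**3. Hand check for 24 h shifts.**
- A stay of length L crosses a shift change with probability L/24, so the share crossing is 5.2/24 = 0.217.
- Crossing stays are length-biased, with mean (5.2² + 3²)/5.2 = 36.04/5.2 = 6.93 h.
- With q = 1, late entrants are 0.5 × 0.217 × 0.5 = 0.0542 of all patients.
- POCUS mean = (0.5 × 5.2 + 0.0542 × 6.93)/0.5542 = 5.37 h.
- Control mean = (0.5 × 5.2 − 0.0542 × 6.93)/0.4458 = 4.99 h.
- Bias = +0.38 h.
- With q = 0.1 the same steps give 5.22 − 5.18 = +0.04 h.

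**4. Simulation, allowing every handover in a stay.** Bias is POCUS minus control, in hours.

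| Shift | Stays crossing a change | q = 10% | q = 25% | q = 50% | q = 100% |
|---|---|---|---|---|---|
| 8 h | 60% | 0.11 | 0.27 | 0.53 | 1.04 |
| 12 h | 43% | 0.07 | 0.18 | 0.37 | 0.75 |
| 24 h | 22% | 0.04 | 0.10 | 0.19 | 0.38 |

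The 24 h row agrees with the hand check. Repeated runs put its lowest cell between 0.03 and 0.04 h. Relative to 1.3 h, the table runs from 0.04/1.3 = 3% to 1.04/1.3 = 80%. If only the first handover can move a patient, the largest cell falls from 1.04 to 0.84 h. Lognormal stays, also with the first handover only, give slightly smaller values (0.75 h for that cell).

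**5. With the planned 25% reduction.** For 12 h shifts and q = 50%, the true 1.3 h appears as about 0.80 h. Power at 84 per group is Φ(0.80/(3 × √(2/84)) − 1.96) = Φ(1.73 − 1.96) = about 41%. The same formula with 1.3 h gives 80%.

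**6. Alternative handling.**
- Group fixed by the first doctor: bias from this route is 0, apart from simulation noise.
- Late-scanned control patients dropped as protocol violations: control still loses long stays, and a bias of about 0.01 to 0.55 h against POCUS remains (first handover only).

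**The case against.** The strongest reply is that the article can be read as assigning patients prospectively. They are assigned consecutively, recruitment stops when each cohort reaches its minimum, and attendance by a trained or untrained professional is an inclusion criterion, normally judged at entry. Consent comes at evaluation, before any study procedure. On that reading the group precedes the scan, a later scan in a control patient is a crossover, and this route is closed. This is a fair reading and may be what is intended. But no sentence ties the group to consent or to the first doctor, and the one sentence on assignment describes the groups by the procedure.

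Second, the article mentions no shift, handover or second doctor, and the 5.2 h mean comes from an outside multicenter trial. This stands in full: the mechanism is possible, not shown, and the sizes above are conditional.

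Third, scan time and operator might be on a case report form that is not shown. That is possible, but the article calls Table 2 complete.

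A reader might infer more than the text supports:
- **That the trial is biased against POCUS.** The direction holds for this route only. A trained doctor's unscanned patients would count as controls under the procedure definition, and that could move the result either way. The simulation leaves them out.
- **That the problem persists even when groups are defined by training alone.** It does so only if any or the last doctor decides. If the first physician decides, it vanishes.
- **That a bias of 30% to 80% of the target is to be expected.** Those figures need every later trained doctor to scan, and nothing in the documents supports that rate.

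**Conclusion.** The point holds as a gap in the group rule. There are two definitions, no moment at which the group is fixed, and no rule for a patient seen by more than one doctor. Table 2 is not the cause; it makes the resulting misclassification undetectable. Grouping by whether a scan was ever done can bias length of stay against POCUS through late scans. Under the assumptions listed, the size with no true effect runs from negligible (about 0.04 h) to most of the planned 1.3 h (about 1.0 h), depending mainly on how often later trained doctors scan and on shift length. The documents do not allow a choice within that range, and they do not settle the net direction once unscanned patients of trained doctors are counted. It is worth correcting because the remedy is cheap and information never recorded cannot be restored at analysis.

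**What to change.** 1. State in the design section that the group is set at consent by the training status of the first physician to assess the patient. State also that length of stay is analysed by that group, whatever happens later. Bring the assignment sentence and Textbox 1 into line with this rule.
2. Make the attending-doctor field the code of that first physician. Add three fields to Table 2 and the case report form: time of first assessment, time of any POCUS, and operator code of any POCUS.
3. Report scans in control patients after a handover as crossover, with their number and timing. Do not use them to form or to empty a group. Report unscanned patients in the experimental group in the same way.

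**Cost.** One sentence and three short fields; no change to care or to the sample size. Crossovers kept in control slightly dilute the contrast. The article says recruitment is under way, so for patients already enrolled the times would have to be recovered from clinical records, if those hold them; where they do not, the number of unclassifiable patients should be reported.

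### Length of stay includes the wait before first physician contact, which comes before exposure, and no planned variable lets a difference in that wait between the non-randomised groups be checked or directly adjusted for

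*Protocol article*

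**What the plan says.** All references are to the protocol article.

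- **Endpoint.** In Variables, Table 2, length of stay is in minutes and is "Calculated from entry and discharge times". The care-process block has two time stamps, "Date or time of arrival" and "Date or time of discharge". The text above the table states: "A complete list of all study variables, including their measurement units or response categories, is provided in Table 2". The table has no time of first physician contact, consent or scan, and no triage level.
- **Group.** In Textbox 1, the experimental group is seen by physicians with demonstrated ultrasound training, and the control group by "professionals without demonstrated training in clinical ultrasound".
- **Entry to the study.** The consent paragraph after Textbox 1 reads: "Informed consent will be obtained by the attending physician at the time of patient evaluation, prior to any study-related procedures".
- **Allocation.** The sample size text in Methods adds: "There will be no randomization of the sample".
- **Planning figures.** The same text takes a mean emergency department stay of 5.2 h (SD 3 h), a 25% reduction (1.3 h), two-sided 5% significance and 80% power, giving 84 per group.
- **Analysis.** Statistical Analysis plans a baseline comparison of the groups, a *t* test on length of stay, and a multiple linear regression adjusting for potential confounders.

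**The concern.** The clock starts at arrival, but the difference between the groups starts only when a physician takes the patient. The interval between the two is inside the endpoint and before exposure. In a randomised comparison it would balance on average and only add noise. Here the group follows the attending physician, so nothing in the design makes the mean wait equal in the two groups.

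If the waits differ, the difference is counted as an effect of the scan. A shorter wait in the scan group would flatter it, and a longer one would hide a real benefit. Because first-contact time is not collected, such a difference could be neither detected nor ruled out from the planned data. This concerns the variable on which the study is sized. Table 3 asks patients separately about the wait for service, the wait for tests and results, and the overall wait, yet the study measures only the total time.

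**Working it through.** **1. The plan's own figure.** Inputs: difference 1.3 h, SD 3 h, two-sided alpha 0.05, power 80%.

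n per group = 2 × (1.960 + 0.842)² × 3² / 1.3² = 83.6, rounded up to 84. The stated 84 is reproduced, with power of 80.2% at that size.

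**2. How the wait enters the estimate.** Write total stay as T = W + P, where W is arrival to first contact and P is contact to discharge. The difference in mean T between groups is the difference in mean W plus the difference in mean P. The scan can act on P only. If mean W is equal in the groups, its term is zero. If not, it is added in full to the unadjusted estimate.

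**3. Size of a difference in the wait.** The target is 1.3 × 60 = 78 min. The documents give no waiting times, so these inputs are assumptions:

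- 10 min: 10/78 = 13% of the target
- 20 min: 20/78 = 26%
- 30 min: 30/78 = 38%

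**4. Effect on the unadjusted test.** With 84 per group and SD 3 h, the standard error is 3 × √(2/84) = 0.463 h. Suppose the scan has no effect and the scan group waits b hours less. The chance of a significant result favouring the scan is then 1 − Φ(1.96 − b/0.463), against a nominal 2.5%:

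- b = 0.25 h (15 min): 7.8%
- b = 0.50 h (30 min): 18.9%
- b = 0.75 h (45 min): 36.7%

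**5. Noise.** If W is independent of P and has an assumed SD of 0.5, 1.0 or 1.5 h, removing it takes the variance from 9 to 8.75, 8 or 6.75 h². The SD falls to 2.96, 2.83 or 2.60 h, and power at 84 per group for an unchanged 1.3 h effect is 81%, 85% or 90%. This is a possible gain over the plan and does not show a shortfall in it: the SD of 3 h is given for emergency department stay, so on that wording the variance of the wait is already in the 84.

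**6. What the planned data can do.** Arrival date and time give hour, weekday and shift of arrival. They do not give the length of the queue at that moment. The attending-doctor code does not help, because each physician belongs to one group only and the code cannot be separated from the group effect.

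**The case against.** The strongest reply is that the endpoint answers the question asked. The objective and the hypothesis concern stay in the emergency department, and arrival to discharge measures that. This stands, and the definition should be kept.

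Second, the mechanism is only a possibility. The article does not say that trained and untrained physicians work different shifts, and Study Design and Setting describes assignment as consecutive. If both kinds of physician draw side by side from one queue, no systematic difference in the wait need arise. This also stands: a reader might infer that the groups are known to differ by shift, but the document does not say so.

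Third, adjustment is already planned. The regression is not limited to patient characteristics, the exact covariates may be left to an analysis plan that is not shown, and hour and shift can be derived from the arrival time stamp. This stands in part. Two patients who arrive at the same hour on different days can face very different queues, and no analysis plan can adjust for an interval that the data set does not hold.

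Fourth, first-contact time may be in the emergency record, so the gap may be recoverable. That is so only if the record holds it, which the document does not say. If it does, the remedy costs less.

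**Conclusion.** The point holds as a limited one. The sizing endpoint of a non-randomised comparison contains an interval before exposure, and Table 2 as listed gives no means to check or directly adjust for a difference in it. On assumed differences of 10 to 30 minutes, the bias would be 13% to 38% of the target effect. With a 30-minute shorter wait in the scan group and no true effect, the unadjusted test would favour the scan in about 19% of studies. Both figures depend on a difference that the document does not show to exist, and whose direction is unknown.

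Three stronger readings are not supported. A reader might infer that waiting time as such is counted as effect; it is not, because equal waits cancel. A reader might infer that length of stay is wrongly defined; it fits the stated objective. A reader might infer that noise from the wait leaves the study too small; the 84 per group reproduces from an SD worded as total stay and is not put in doubt.

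**What to change.** Add the time of first physician contact to Table 2 and keep arrival-to-discharge as the endpoint. Then:

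1. Compare arrival-to-contact time between the groups as part of the baseline comparison already planned.
2. Enter it as a covariate in the planned linear regression for total stay, together with hour or shift of arrival derived from the existing time stamp.
3. Report contact-to-discharge time by group as a supporting analysis, without the wait as a covariate. With the wait in the model, the group coefficient is algebraically the same for total stay and for contact-to-discharge time, so the supporting result would add nothing.

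The cost is one time stamp and a covariate or two; no clinical procedure changes. The drawback is missing data. The Results section describes recruitment as under way and due to finish in December 2025, so the value must be taken from the emergency record for patients already enrolled, and it will be missing for them if the record does not hold it. The number missing should be reported by group. Any gain in precision is a bonus that depends on the assumed SD of the wait.

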**Methods:**

This is a pilot quasi-experimental study assessing feasibility and viability, with a nonrandomized control group, to be conducted in the Emergency Department of Hospital Comarcal de Riotinto. Adult patients (≥18 y) presenting with abdominal pain will be included. Both groups will receive standard care. In the intervention group, bedside ultrasound will be performed by trained family physicians; in the control group, ultrasound will be performed by radiologists only if deemed necessary. The primary outcome is the improvement in quality of care, assessed through a reduction in emergency department length of stay, fewer basic radiology tests requested, and diagnostic concordance. Secondary outcomes include the need for additional diagnostic studies and the appropriateness of referrals, evaluated through 1-month follow-up and reconsultation.

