**Conclusions:**

This study aims to demonstrate the clinical and organizational benefits of implementing bedside ultrasound by family physicians in emergency care.

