To achieve the target sample size, recruitment will be conducted consecutively among eligible patients presenting with abdominal pain at the Emergency Department. All family physicians participating in the study have been informed and trained to identify and invite potential participants. The collaboration of the entire emergency care team will be essential to ensure continuous enrollment during the study period. Regular follow-up meetings will be held to monitor recruitment progress and address potential barriers.

Prior to this, training will be provided to professionals, and a common understanding will be reached on the possible main findings. This is intended to reduce clinical variability and improve the external validity of the study.

Given the limited sample size, short duration, and minimal risk involved in this pilot quasi-experimental study, a formal independent data monitoring committee has not been established. The principal investigator and the co-investigators will be responsible for monitoring trial conduct, data accuracy, and participant safety. As no data monitoring committee is planned, further details regarding its charter are not applicable.

No interim analyses are planned for this study due to its exploratory nature and short timeframe. Consequently, no predefined stopping rules have been established. The final decision to complete or terminate the study will rest with the principal investigator, based on recruitment feasibility, protocol adherence, or unforeseen safety concerns.

To ensure data integrity, a quality control procedure has been designed, including predefined field validation rules within the case report form. Participating clinicians were trained during project initiation to minimize data entry errors. Data entry will follow the case report form sequence, and filters will prompt the confirmation of extreme or illogical values. The principal investigator will perform monthly audits, and a second investigator will periodically review the database or a sample of its records. Questionnaire variables will be coded numerically, and preliminary analyses will be performed to detect inconsistencies or missing data. All efforts will focus on minimizing missing data and correcting errors promptly to reduce potential biases and ensure the reliability of the findings.

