**Figure 1. F1:**
[figure not shown]
Flowchart depicting study protocol. POCUS: point-of-care ultrasound.

Subjects will be observed for a period of 1 month to determine whether they have returned for a repeat consultation for the same reason, and if so, to check the degree of alignment of the final diagnosis with the initial care. Only in cases where the process is not resolved can the patient be monitored for the next 6 months.

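### Diagnostic concordance is a yes/no judgement with no stated criterion or assessor masking, stored beside variables that reveal the group, so borderline cases are open to assessor bias of unknown direction and size

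*Protocol article*

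**What the plan says.** The abstract's Methods defines the primary outcome as improved quality of care, assessed through shorter length of stay, "fewer basic radiology tests requested, and diagnostic concordance". The Variables section lists among the main outcome variables "the performance of bedside ultrasound (POCUS), diagnostic concordance" and satisfaction. Study Design and Setting is less emphatic. Its primary objective covers length of stay, simple radiology and further radiodiagnostic examinations, and concordance analyses come later among the additional aims.

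Table 2 gives concordance a binary format, "Yes or no (based on follow-up or second opinion". The text after Figure 1 describes a one-month observation for repeat consultation and, where one occurs, a check "to check the degree of alignment of the final diagnosis with the initial care". The abstract's secondary outcomes include "the appropriateness of referrals, evaluated through 1-month follow-up and reconsultation".

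Table 2 also holds fields for POCUS performed, POCUS findings and the attending doctor ("Family physician ID"). In Textbox 1 the treating physician's ultrasound training defines the group. Table 2 is presented as the full list of study variables. Its only diagnosis field is the final emergency department diagnosis, in free text or ICD-10. It has no field for a follow-up diagnosis and none for referral appropriateness.

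On oversight, the principal investigator audits monthly and "a second investigator will periodically review the database or a sample of its records". No section mentions masking of any outcome assessor.

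**The concern.** Care cannot be blinded here, because the treating physician performs the scan and that physician's training defines the group. Concordance is different. It is judged afterwards, by comparing an earlier diagnosis with a later one, and that comparison can be made without knowing the group.

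As the article stands, nothing keeps the group from whoever makes the judgement, and no rule limits discretion. A case first labelled nonspecific pain and later given a specific diagnosis could be scored either way. The reference may be follow-up or a second opinion, which adds discretion. A modest lean in such cases would produce a group difference that cannot be told from a real one. Neither the regression adjustment nor the Holm-Bonferroni correction in Statistical Analysis addresses an error in the outcome itself. As listed, the data set would not store the follow-up diagnosis, so the judgement could not be re-scored from it.

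The problem is separate from which patients are verified: it would remain if every patient had the same reference diagnosis.

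**Working it through.** **The plan's own figure.** The article gives no concordance rate or target difference; its only sample-size calculation is for length of stay. With a difference of 1.3 h, SD 3 h, two-sided 0.05 and 80% power, n = 2 × (1.96 + 0.84)² × 3² / 1.3² ≈ 84 per group, as stated. With 15% added, 84 × 1.15 = 96.6, hence 97 per group and 194 in total. The point does not depend on this calculation; 84 is used below only as the number analysed per group.

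**Does the record reveal the group?** Group follows from the physician's training (Textbox 1), so the physician code reveals it. The POCUS performed and POCUS findings fields reveal it directly. All three are in the same variable set as concordance.

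**Illustration 1: nonspecific cases.**
- Share open to judgement: 24% to 44%, the frequency of nonspecific pain that the Introduction quotes from a review. Treating all of these as open to judgement is an assumption.
- Called concordant: 60% in one group, 40% in the other. This is an assumption.
- Spurious difference: 0.24 × (0.60 − 0.40) = 0.048, and 0.44 × 0.20 = 0.088. That is 4.8 to 8.8 percentage points.

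If alignment is checked only in patients who return, this is multiplied by the return rate, which the article does not give. Assuming 10%: 0.10 × 4.8 = 0.5 to 0.10 × 8.8 = 0.9 points. Assuming 30%: 0.30 × 4.8 = 1.4 to 0.30 × 8.8 = 2.6 points.

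**Illustration 2: chance of a false finding.** Suppose true concordance p is equal in both groups, all 84 per group are judged, and a fraction f of discordant POCUS cases is scored as concordant. The observed POCUS rate is then p + f(1 − p), and the spurious difference is d = f(1 − p). The chance of a significant result favouring POCUS is Φ[(d − 1.96 × SE₀)/SE₁], with SE₀ from the pooled rate and SE₁ from the two separate rates.

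Worked case, p = 0.80 and f = 0.25: the POCUS rate is 0.85 and d = 0.05. SE₀ = √(2 × 0.825 × 0.175/84) = 0.0586. SE₁ = √((0.85 × 0.15 + 0.80 × 0.20)/84) = 0.0585. Then (0.05 − 0.1149)/0.0585 = −1.11, and Φ = 0.13.

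| True rate | f = 10% | f = 25% | f = 50% |
|---|---|---|---|
| 0.70 | 3 points, 6% | 7.5 points, 20% | 15 points, 65% |
| 0.80 | 2 points, 5% | 5 points, 13% | 10 points, 44% |
| 0.90 | 1 point, 4% | 2.5 points, 8% | 5 points, 23% |

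With no differential judgement the chance is 2.5%. At a first Holm step of 0.05/3 (assuming three hypotheses), the f = 25% and f = 50% entries at p = 0.80 become 6% and 28%, against 0.05/3/2 = 0.8% without bias. The correction lowers the error but does not remove the bias. The direction is chosen for illustration; a lean against POCUS would work the same way in reverse.

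**What is not affected.** Length of stay is computed from time stamps, and test counts are not adjudicated.

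**The case against.** The strongest reply is that this rests largely on silence in a condensed article. Table 2 lists what is stored, not what an assessor sees. A second opinion could mean a separate judge, and the full protocol may say more. This stands in part: a reader might infer that assessors will know the group, but the article does not say so. What remains is that the stated measurement is a yes/no with two alternative reference sources, no criterion and, in the listed variables, no stored follow-up diagnosis.

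A reader might also infer a lean towards POCUS from the abstract's Conclusions: "This study aims to demonstrate the clinical and organizational benefits of implementing bedside ultrasound by family physicians in emergency care". Elsewhere the aim is to assess or analyse the impact, so that sentence does not establish direction.

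Concordance has less weight in the objectives than in the abstract, and it does not drive the sample size. That stands and limits the consequence, but it does not remove concordance from the abstract's primary outcome.

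Diagnoses may be ICD-10 coded, which narrows discretion. However, free text is equally permitted, and no rule says when two codes agree.

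Referral appropriateness rests partly on reconsultation, an observable event. Only the step from that event to a judgement of appropriateness is subjective, so the concern is weaker there.

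Finally, the numerical illustrations use assumed splits. That stands in full.

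**Conclusion.** The point holds as a weakness in how concordance is measured, not as a demonstrated bias. Following the article as written leaves a judged component of the primary outcome without a criterion or masking, next to fields that reveal the group. An assessor who sees those fields could favour either group in borderline cases.

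Neither the direction nor the size can be derived from the documents. The 5 to 9 points should not be read as an estimate. They assume that every nonspecific case is judged and that the split is 60/40, and they fall to roughly 0.5 to 2.6 points if only an assumed 10% to 30% of patients return and only those are checked. The false-finding rates of 4% to 65% likewise depend on assumed true rates and assumed upgrading. The change is worth making because it is cheap, alters neither care nor sample size, and can be applied to patients already enrolled.

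**What to change.** - Record the follow-up diagnosis as its own field, with its source.
- Score concordance in both groups by one written rule fixed beforehand, for example same ICD-10 category.
- Score from a REDCap export that shows only the index emergency department diagnosis and the follow-up diagnosis. Hide group, physician code, both POCUS fields and radiology tests.
- Use an existing co-investigator who neither treated the patient nor reviewed that record unmasked. The second investigator who checks the database may already have seen the group, so that person is suitable only for records not yet reviewed.
- For referral appropriateness, either report the observable reconsultation outcome or score it masked by a prespecified rule.
- State whether concordance is assessed in all patients or only in those who return.

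The cost is one added field, one export view and a few minutes per record for about 194 records, with no new staff. Scoring every record is a new task compared with a periodic check of a sample. Free text will occasionally unmask the scorer; noting when this happens allows a sensitivity analysis without those records.
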